#### **8.1.5. Previous experience of the research group in teaching the CCT to medical students.**

The results found by us in the Teaching Innovation Project of the UCM for the 2019-20 academic year (PID nº 334, precedent of the present study collected in PID nº 139 2020-21) coincide with findings from the literature (Weingartner, 2019). In this preliminary study, our students significantly increased: i) their sense of shared humanity; (ii) all parameters related to mindfulness; (iii) the ability to remain in the face of discomfort without distress and; iv) self-friendliness (unpublished data, collected in the memory of PID nº 339 2019-20). In summary, the skills learned helped them reduce the stress associated with their personal and academic lives, and reinforce their personal and patient interactions.

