#### **8.4. Hypothesis**

1. The standardized Compassion Cultivation Training (CCT) program will produce an improvement in emotional well-being and a reduction in psychological distress (stress, anxiety, depression) and burnout of post-program medical students compared to a control group on the waiting list.
2. Such changes shall be maintained over time two and six months after the end of the programme.
3. The above changes will be driven by increases in compassion for oneself, compassion for others, attention to the present moment, and emotional regulation skills.
4. The skills developed in the program will be a protective factor for the management of stress and psychological distress caused by the COVID-19 pandemic.

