**Figure 1. CONSORT diagram**

In a **first phase**, participants will be randomized into the two study groups (Fig. 1): experimental group (i.e., CCT program) or control group on waiting list. Such randomization shall be carried out after baseline assessment to avoid the occurrence of biases produced by expectations of participation in the CCT® program.

In a **second phase**, 2 months after the end of the first CST programme (CST-1), in February 2021, participants on the waiting list will be offered the possibility of participating in the CST programme by becoming the CCT-2® group.

People who voluntarily want to participate in the research will commit to carry out a pre-program® evaluation, a brief inter-sessional evaluations during the program, an evaluation at the end of the program and an evaluation at 2 and 6 months after the end of the program. During the first phase of the study, the waiting list group (control group) will undergo the same evaluations and at the same times as the CCT-1 group.

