#### **14. STATISTICAL ANALYSIS**

Following the CONSORT recommendations, Intention-To-Treat Analysis will be performed to handle lost data. A diagnosis of the randomness pattern of the loss will begin using Little's MCAR test. The baseline differences between completers (i.e., per-protocol) and missing will also be analyzed to determine if there are any variables in the dataset that predict data loss. Depending on the loss pattern, multiple imputations will be made or by means of Maximum Likelihood algorithms. Finally, sensitivity analyses will be performed comparing the per-protocol data with the imputed ones to determine if the imputation has generated biased estimates. As indicated in the previous section, the criterion of attendance at 75% of the sessions of the program will be used as an indicator of "minimal exposure to treatment".

Student's t-tests and chi-square tests will be used to analyze differences between groups at baseline. The main analysis will be a mixed ANOVA with two factors: independent measures group factor (experimental vs control) and repeated measures time factor (pre, post, follow-up 2 and 6 months). ANCOVAs will also be performed using baseline as a covariate in analyses and repeated measure ANOVAs to assess the maintenance of changes over time. The analysis of variance will be complemented by mediating and moderating analyses to study the mechanisms of change of the program. A significance

level of alpha 0.05 will be defined in bilateral contrasts. Statistical analyses will be carried out using SPSS (v. 25) and R (v. 3.6.1) software.

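### At 6 months the waiting list may already be trained, so neither the group contrast nor the within-group change can show by itself that the benefit is maintained; the 2-month comparison is sound

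*Protocol*

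**What the plan says.** The maintenance claim is in section 8.4, hypothesis 2: "Such changes shall be maintained over time two and six months after the end of the programme". Secondary objective 1 in section 10 repeats it.

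Section 14 gives two analyses that bear on it. One is the main model: "The main analysis will be a mixed ANOVA with two factors: independent measures group factor (experimental vs control", crossed with a "repeated measures time factor (pre, post, follow-up 2 and 6 months". The other is listed separately, after the baseline-adjusted ANCOVAs: "repeated measure ANOVAs to assess the maintenance of changes over time". No group is named for this second analysis.

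The design text under Figure 1 (section 9.1) says that two months after the first programme ends, "participants on the waiting list will be offered the possibility of participating in the CST programme by becoming the CCT-2" group. It commits participants to "an evaluation at 2 and 6 months after the end of the program". It promises that controls are assessed at the same times as CCT-1 during the first phase. Section 11.2 sets the programme at 8 weekly meetings. Section 14 mentions neither CCT-2 nor the change in the controls' status.

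**The concern.** The control group is untrained up to the 2-month visit but may be trained by the 6-month visit. Section 14 treats the four time points alike, as if the control meant the same thing at each.

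Two misreadings follow at 6 months. If maintenance is judged from change within CCT-1, loss of effect cannot be told apart from whatever the period does to every student. The protocol itself ties its outcomes to such conditions: hypothesis 4 concerns "stress and psychological distress caused by the COVID-19 pandemic", and section 8.1.5 reports that the skills helped students to "reduce the stress associated with their personal and academic lives". If maintenance is judged from the group contrast, two trained groups are compared, and a fully kept benefit looks like no difference from control.

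The 6-month half of hypothesis 2 and of secondary objective 1 can therefore be answered wrongly in either direction.

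**Working it through.** **1. Timing, counted from the end of CCT-1.** CCT-2 is offered at 2 months and lasts 8 weeks: 8 × 7 / 30.44 = 1.84 months.
- If CCT-2 starts when offered, it ends at 2 + 1.84 = 3.84 months, before CCT-1's 6-month visit.
- CCT-2's own 2-month visit falls at 3.84 + 2 = 5.84 months, about 0.16 × 30.44 ≈ 5 days before CCT-1's 6-month visit.
- CCT-2's own 6-month visit falls at 3.84 + 6 = 9.84 months, on a much later date.

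The mention of February 2021 can date either the end of CCT-1 or the offer. The intervals are the same under both readings.

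**2. The plan's own sample size.** Section 13.1 gives an effect size of 0.40, alpha 0.05, power 90% and N = 44, without naming the metric. Read as Cohen's f for the between-groups effect, with m = 4 visits and correlation ρ = 0.5 (both assumed), λ = N f² m / (1 + (m − 1)ρ) = 44 × 0.16 × 4 / 2.5 = 11.26 on 1 and 42 df. The power is 0.906, and 44 is the smallest even N that reaches 90%. For two equal groups f = 0.40 corresponds to 2 × 0.40 = 0.80 SD. Read as a standardised difference of 0.40, a two-sample comparison would need 132 per arm. The illustrations below therefore use 0.80 SD, with 22 per arm and ρ = 0.5 unless stated.

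**3. Within-group change.** Let E2 and E6 be the benefit at 2 and 6 months, and c the calendar shift common to all students between those visits. The expected change in CCT-1 is (E6 − E2) + c, so c enters one for one. Its standard error is √(2(1 − ρ)/22) = √(1/22) = 0.21 SD. With the benefit fully kept (E6 = E2), a paired two-sided 5% test is significant as follows:

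| Shared shift c (SD) | 0 | 0.1 | 0.2 | 0.3 | 0.4 | 0.5 |
|---|---|---|---|---|---|---|
| Trials showing a significant change | 5% | 7% | 15% | 27% | 43% | 61% |

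At c = 0.5 the figure is 47% with ρ = 0.3 and 82% with ρ = 0.7. In the other direction, if a 0.80 SD benefit is fully lost but the period favours everyone by 0.5 SD, 61% of trials still show a significant gain from baseline to 6 months.

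**4. The group contrast.**
- At 2 months the control is untrained and c cancels. In simulation the difference in change was 0.80 (SE 0.30), which is unbiased.
- At about 6 months, if a fraction u of controls has taken CCT-2 and its 2-month effect equals CCT-1's, the contrast is (E6 + c) − (u·E2 + c) = E6 − u·E2. With u = 1 and E2 = 0.80 it is 0.00 when the benefit is fully kept and −0.80 when it is fully lost. With u = 0.5 and the benefit kept it is 0.80 − 0.40 = 0.40. None of these is the effect against no training.
- If the model instead takes CCT-2's own 6-month visit as the control value, the dates no longer match and c does not cancel.

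**5. What the same-date contrast can give.** Comparing CCT-1 at 6 months with CCT-2 at its 2-month visit cancels c, and the simulated error rate was 5%. Adjusted for baseline, its SE is √(2(1 − ρ²)/22) = √(1.5/22) = 0.26 SD (0.27 in simulation). Adding the randomised 2-month contrast gives a 6-month effect. Given baseline, each visit has variance 0.75 and the two have covariance 0.25, so the sum has variance 0.75 + 0.75 + 2 × 0.25 = 2.0 and SE √(2 × 2.0/22) = 0.43 SD. On unadjusted sums the simulated SE was 0.52.

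**The case against.** The main model does include the control group at every visit, and section 14 names no group for the repeated-measures ANOVAs. A reader might infer that maintenance as a whole is judged only within the trained group. The documents do not support that. The within-group reading is the natural one, since these ANOVAs are listed apart from the model with the group factor, but it remains an inference. At 2 months the comparison is randomised, on the same date and against untrained students, so half of hypothesis 2 is protected. This stands, and it confines the point to 6 months.

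A reader might also infer that CCT-2's 2-month visit supplies a clean comparison that removes the problem and should replace the planned analysis. It does not. The arms also differ in cohort, in the period when they were trained and in length of wait, and CCT-2 is only offered. The contrast measures loss from 2 to 6 months, not from post. If a 0.80 SD benefit decayed exponentially to a quarter at 6 months, 0.80 × 0.25^(1/3) = 0.50 would remain at 2 months; the contrast would return 0.50 − 0.20 = 0.30, against a true loss since post of 0.60. With 22 per arm a loss of 0.30 SD would be significant in only about 20% of trials. This too stands, so the contrast can be supportive only.

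A third tempting reading takes the 0.40 of section 13.1 as a 0.40 SD benefit, so that a 0.40 SD drift would cancel the whole effect. The sample-size check does not support that reading.

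Finally, how CCT-2 data enter a model could be left to an analysis plan that is not shown. But the protocol already fixes a control factor through 6 months and a test for maintenance, and as fixed these do not match its own design.

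**Conclusion.** The point holds for the 6-month part of hypothesis 2 and secondary objective 1, and for that part only. For controls who take up CCT-2 there is no untrained concurrent comparison at 6 months. The group contrast there approximates the 6-month effect minus the 2-month effect, and the within-group change carries any shared shift in full.

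That structure follows from the protocol's own schedule, provided that CCT-2 starts when offered and controls take it up. The error rates of 27% and 61% rest on assumed shifts of 0.3 and 0.5 SD and a correlation of 0.5; the documents give neither. Controlled results at post and 2 months are not in doubt, and the stated sample size is not the issue.

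**What to change.** In section 14:

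1. Base the controlled efficacy and maintenance claim on pre, post and 2 months. State that the 6-month group contrast is not to be read as treated versus untreated.
2. Name the group for the repeated-measures ANOVAs, and report CCT-1's change to 6 months as uncontrolled and descriptive.
3. Add, as a supportive analysis, a baseline-adjusted comparison of the arms as randomised at the near-common date when CCT-1 is 6 months and CCT-2 about 2 months past training. Interpret it as loss from 2 to 6 months only if the 2-month effect can be taken as equal in both cohorts and CCT-2 uptake is high. Report uptake alongside it.
4. Report the contrast, and any summed 6-month effect, as an estimate with its interval rather than as a test.

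The cost is wording plus one further ANCOVA on evaluations that participants already commit to. The real price is a weaker 6-month claim with low precision: at correlation 0.5 and a critical t of about 2.02, the 95% half-width is about 2.02 × 0.26 = 0.53 SD for the contrast and 2.02 × 0.43 = 0.87 SD for the summed effect.

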## **15. ETHICAL CONSIDERATIONS**

Given the nature of the study that is presented for evaluation by the Ethics Committee, the research team will follow at all times during the development of the trial the ethical standards set by the Code of Ethics of the Psychologist published by the Official College of Psychologists (<https://www.cop.es/pdf/Codigo-Deontologico-Consejo-Adaptacion-Ley-Omnibus.pdf>). Research participants shall not be exposed to any permanent, irreversible or unnecessary harm, and their participation in the research shall be explicitly authorised by informed consent (Art. 34). Likewise, the research will respect the dignity of people, their beliefs, their privacy and their modesty (art. 37). Regarding the use of the information, only the information strictly necessary for the performance of the tasks and always with the express authorization of the participants in the research will be collected (art. 39).

All information obtained will be subject to the duty and right of professional secrecy (art. 40) and will be treated with absolute confidentiality, maintaining the anonymity of the participants in any publication to which the project could give rise. In any case, all the members of this project will adapt to the provisions of Organic Law 3/2018 of December 5 on the Protection of Personal Data and Royal Decree 1720/2007, of December 21, which develops said Law.

The study that is proposed for evaluation by the Committee, supposes a practically non-existent risk for the participant since during the development of the program, he will be repeatedly warned to prioritize his well-being over the recommended practices and exercises as well as to perform them within an emotional safety zone, being encouraged to suspend them and consult the instructor before any incident. The instructor will be available to participants throughout the duration of the study via email, personal telephone or online videoconference to meet the needs of the participants. In addition, during all online sessions and following the recommendations of the Compassion Institute to offer the CCT® program online, and in order to better monitor the participants by the instructor during online connections, he will preferably be assisted by another person in the technical issues of the connection. In this study, this work will be carried out by a sixth-grade medical student member of the Teaching Innovation Project in which this study is framed.

The present clinical trial uses questionnaires and extended measures used in clinical and psychological research (see section 9.2.1) and meditation (mainly attentional and phenomenological aspects). All participants are volunteers and if a high score is observed in the depression or anxiety questionnaires, they will be informed of the availability of assistance services, if they wish, both in the Faculty of Psychology of the UCM and in the field of the public health system. The participation in the project team
